### Data management

All the completed survey questionnaires are reviewed by a research team member for missing data and unusual responses. Data are double entered into an SPSS (version 21.0) database; after completing entry, the two databases will be reconciled to minimize data entry related errors.

The research team directly enters the data collected during daily calls made to the supporting family members of patients in the intervention arm into an Epi-info database.

The complete de-identified dataset of the trial will be publicly available when finalized.

### Statistical analyses

Statistical analyses will follow the intention-to-treat principle [46]. We will assess randomization across the two arms by comparing sociodemographic characteristics and other potential confounding variables using chi-square for binary and categorical variables, t-test, or other equivalent nonparametric tests, as appropriate, for continuous variables.

The primary outcome (treatment outcome) will be analyzed using generalized mixed effect model applying binomial distribution, logistic regression [47]. The status of randomization (intervention/control) will be included as an independent variable; to account for the clustered design we will treat clusters as a random effect. Potential confounding variables (age, gender, socioeconomic status, and others) with significant differences across intervention and control arms will be included as fixed factors. Secondary outcomes including knowledge, depression status, quality of life, within family TB-related stigma, and family social support also will be tested using generalized linear mixed effect models using logistic regression or linear regression, as appropriate. The secondary outcome model also will include its baseline assessment as a covariate.

We will report all the descriptive and inferential statistics results with their 95 % confidence intervals.

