## Methods/design

### Trial design

This is an open-label, stratified cluster randomized controlled superiority trial with two parallel equal arms (intervention and control) conducted in Armenia. TB outpatient centers defined the clusters, with equal numbers of clusters assigned to intervention and control arms. We performed a cluster-level random assignment of drug sensitive TB patients to intervention and control arms to mitigate potential contamination of participants in the control arm.

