### Outcomes and additional measurements

The primary outcome of this controlled trial is TB treatment outcome according to WHO definitions as recorded in the medical file and reported to the NTC. Treatment outcomes are classified as follows: cured, completed treatment, dead, failed, defaulted, and transferred [35]. A patient is considered to be successfully treated if he/she has a cured or completed treatment outcome. All other categories are considered as an unsuccessful treatment outcome.

Secondary outcome measures include patients’ knowledge, depression status, quality of life, within-family TB-related stigma, family social support, and self-reported adherence to TB treatment. In addition, we measure family members’ knowledge, depression status, social support toward TB patient, and TB-related stigma. All the secondary outcomes other than self-reported treatment adherence are measured at T0 (baseline) and T1 (follow-up). Self-reported treatment adherence is assessed only at T1. The knowledge variable is constructed from correct responses to five items adapted from previous work [36–38]. Depression is assessed using a modified version of the Center for Epidemiological Studies Depression (CES-D) scale [39]; the Armenian translation is validated and the negatively formulated 16 items show high diagnostic accuracy and good factorial structure [40, 41]. We have used a modified version of a validated scale to measure within-family TB related stigma [42] and the Berlin social support scale [43] to measure social support of family members toward TB patients. We have applied EQ-5D to obtain data on quality of life of patients [44].

Measurements on sociodemographic characteristics including age, gender, socioeconomic status, education, marital status, and health behavior (smoking and drinking) are obtained to verify the validity of randomization and, if necessary, to control for the potentially confounding effects of these variables on the primary and secondary outcomes. Table 1 summarizes the study outcomes and presents the frequency of data collection.

**Table 1 Tab1:** Outcome variables

			Timeline	
Variable	Source	Type	T0^a^	T1^b^
Treatment outcomes	National Tuberculosis Control Center reported treatment outcome evaluation	Categorical		X
Possible Depression	Patient survey	Continues	X	X
Quality of life	Patient survey	Continues	X	X
TB knowledge	Patient survey	Continues	X	X
TB-related stigma within family	Patient survey	Continues	X	X

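### Covariates enter the primary model only if they differ significantly between arms, judged by tests that ignore clustering; the model should be fixed in advance on prognosis

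*Protocol article*

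**What the plan says.** In the protocol article, Statistical analyses first proposes to assess randomisation by comparing the arms "using chi-square for binary and categorical variables, t-test, or other equivalent nonparametric tests, as appropriate, for continuous variables". It then gives the entry rule for the primary model: "Potential confounding variables (age, gender, socioeconomic status, and others) with significant differences across intervention and control arms will be included as fixed factors". Outcomes and additional measurements agrees: sociodemographic and behavioural data are "obtained to verify the validity of randomization and, if necessary, to control for the potentially confounding effects of these variables". That section names seven such variables: age, gender, socioeconomic status, education, marital status, smoking and drinking.

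Clustering is dealt with only in the outcome model, where "to account for the clustered design we will treat clusters as a random effect". No cluster adjustment is named for the baseline tests, although under Trial design "TB outpatient centers defined the clusters, with equal numbers of clusters assigned to intervention and control arms". The stratification factors, 2012 patient load and center performance, are not listed in the primary model. For secondary outcomes, by contrast, the baseline value is a covariate fixed in advance.

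**The concern.** There are four difficulties.

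- A p-value for baseline imbalance carries no information on whether a variable predicts treatment success. A strong predictor with a non-significant difference is left out; a weak one with a significant difference goes in.
- Patients within a center resemble one another, and whole centers were allocated. A patient-level chi-square or t-test treats them as independent, so its p-values tend to be too small.
- The primary model cannot be written down before the baseline data are seen. The list ends in an unspecified remainder and the threshold is not stated.
- A logistic odds ratio is conditional on the covariates in the model, so the quantity estimated depends on which imbalances happen to arise.

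At stake are the prespecification of the primary estimate and the precision that known predictors could supply.

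**Working it through.** **Inputs from the protocol article.** 26 centers per arm, 52 in all (Assignment of intervention/randomization). 190 patients per arm, which is 95 × 2 (Sample size). ICC 0.04, stated for treatment outcome (Sample size). Three covariates named in Statistical analyses and seven in Outcomes and additional measurements. The plan gives no figure of its own for the behaviour of the screen.

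**Assumptions.** Baseline tests at two-sided 5%; equal center sizes; independent covariates; a covariate ICC of 0.04, borrowed from the outcome, with 0.01 and 0.10 as a range.

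**Step 1: size of one baseline test.**
- Patients per center: m = 380/52 = 7.3.
- Design effect: DE = 1 + (m − 1) × ICC = 1 + 6.31 × 0.04 = 1.25.
- True size of a nominal 5% test: 2 × [1 − Φ(1.96/√DE)] = 2 × [1 − Φ(1.75)] = 0.080.

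**Step 2: chance that at least one of k null covariates is flagged.** 1 − (1 − a)^k, with a from step 1:

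| Covariate ICC | DE | Size a | k = 3 | k = 7 |
|---|---|---|---|---|
| Valid 5% test | 1 | 5.0% | 14% | 30% |
| 0.01 | 1.06 | 5.7% | 16% | 34% |
| 0.04 | 1.25 | 8.0% | 22% | 44% |
| 0.10 | 1.63 | 12.5% | 33% | 61% |

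At ICC 0.04 and k = 7, clustering adds 44 − 30 = 14 points; the other 30 are ordinary multiplicity.

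**Step 3: effect on the treatment comparison.** A simulation used 52 centers averaging 7.3 patients, with varying sizes. There were seven covariates with ICC 0.04, one of them prognostic (assumed log-odds 1.0 per SD), an outcome ICC of 0.04, and 3,000 trials per scenario. Cluster-robust standard errors stood in for the planned mixed model.

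| | Selection rule | Unadjusted | Prognostic covariate prespecified |
|---|---|---|---|
| Type I error, no treatment effect | 4.0% | 4.5% | 4.6% |
| Power, treatment log-odds ratio 0.8 | 67% | 67% | 72% |
| Mean estimated log-odds ratio, same scenario | 0.70 | 0.69 | 0.80 |

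The prognostic covariate was selected in about 9% of trials, against 8 to 9% over all seven, so the rule did not favour it. The last row shows how the estimated odds ratio depends on the covariate set.

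**The case against.** The strongest reply is that the rule does little harm to the primary test. It uses only baseline data and arm, never outcomes, and for the named variables it is mechanical. The real discretion lies in the open list and the missing threshold, which an analysis plan not shown here could settle. This stands in part: it limits the seriousness. It does not rescue the rule, which the protocol states outright and which would still select on imbalance if both gaps were closed.

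A reader might infer from the screening-test figures that the primary p-value is invalid. The evidence does not support that: the figures in step 2 describe the baseline screen only, and step 3 shows no inflation for treatment.

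A reader might also take every flagged variable to be a chance finding. The documents do not allow this. Under Recruitment, physicians report patients, who then consent, after centers have been allocated without blinding, so some imbalance may be real recruitment bias, for which adjustment is reasonable. A significance screen, however, does not reliably detect or remove such bias.

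Third, the Background contrast between new and previously treated patients might seem to establish treatment history as prognostic. It does not: the figures there (3.6% and 20%) are prevalences of multidrug-resistant disease, while this trial enrols drug-sensitive patients. Both groups are enrolled (Recruitment), so treatment history is a candidate covariate, no more.

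Finally, the percentages rest on favourable choices. Seven covariates is the longer list, and correlated covariates, such as education with socioeconomic status, would lower the joint figures. This is accepted, and the lower figures for three covariates are given beside the higher ones.

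**Conclusion.** The concern holds as a weakness that should be fixed, not as a flaw that invalidates the primary test. The stated rule selects on imbalance rather than prognosis, uses tests that ignore the cluster randomisation, and leaves the primary model and its conditional odds ratio open until baseline data are seen.

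At an assumed covariate ICC of 0.04 and a 5% level, each null covariate is flagged about 8% of the time. At least one of three to seven is flagged in about 22 to 44% of trials, against 14 to 30% for valid tests. The joint figures are upper bounds as regards correlation among the covariates. Unequal center sizes push slightly the other way: the simulation, with varying sizes, gave 44% and 47.5% for seven covariates in its two scenarios. The protocol's 0.04 is for the outcome, so its use for covariates is an assumption.

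The demonstrated cost to the treatment comparison is lost precision: about 5 points of power (67% against 72%) in one illustration with a strong assumed predictor.

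**What to change.** Delete the significance rule and the tests of randomisation. Prespecify the primary model as:

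- arm, with center as a random effect;
- the stratification factors, patient load and performance, entered parsimoniously;
- a very short list of covariates chosen on prognostic grounds (for example age and sex, with treatment history as a candidate), entered whatever the observed balance.

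Report baseline characteristics by arm descriptively. Label any adjustment prompted by observed imbalance a sensitivity analysis.

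The change is to wording; age and gender are already collected, and the trial was still enrolling when the article was submitted. The price is model parameters when unsuccessful outcomes may be few. Arm (1), load (2), performance (2), age, sex and treatment history make 8. The protocol gives no comparator success rate, so the event count must be assumed. At 88.5% against 98.5%, one pair of rates that reproduces its 95 with a two-sided test, 190 × (0.115 + 0.015) ≈ 25 events, about 3 per parameter. At 80% against 90%, 190 × (0.20 + 0.10) = 57, about 7 per parameter. The list must therefore stay short.

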### Patient safety and monitoring of adverse events

TB patients included in this trial are drug-sensitive and have completed their intensive treatment phase. We take special efforts to minimize potential adverse events. All patients in the intervention arm undergo routine medical check-ups during weekly visits to TB outpatient centers. Moreover, the side effect report form is completed daily and reported by telephone to the research team, allowing the research team to quickly report concerns to the corresponding TB physician for follow-up. Side effects among those patients in the control arm are taken care during their regular daily visits to TB outpatient centers.

### Research ethics

The American University of Armenia Institutional Review Board (IRB) reviewed and approved the study protocol (# AUA-2014-020). Study-related activities started only after receiving IRB approval.

In this multicomponent intervention, we randomized at the TB outpatient center (cluster) level. Individual patient assignments therefore are determined by their geographically assigned TB outpatient center. Patients (and their family members) can only participate in the intervention arm after reading and signing a written consent form. Patients opting out of their assignment and those in the control arm receive traditional DOT for the continuous phase of TB treatment.

### Data safety

All patients are assigned a unique ID. The questionnaires and other data collection forms contain no identifiable information. Hardcopy questionnaires are stored in a locked safe in the research center at the American University of Armenia School of Public Health and will be archived for at least three years. Electronic databases are password protected and select members of the research team have access to the databases. No identifiable information is provided to persons outside the research team.

## Discussion

TB poses a major burden on populations, particularly among those living in low- and middle- income countries. Any improvement in TB treatment strategies can have a significant public health and economic importance. Improved control and management of TB can lead to better treatment outcomes, thereby decreasing health inequalities, morbidity, mortality, and economic costs associated with the disease. Rigorously evaluated alternative people-centered strategies, if successful, can be implemented in countries with similar healthcare and economic profiles and help to forestall TB and multidrug-resistant TB epidemics.

### Trial status

At the time of submission of this manuscript, the trial is ongoing; it began enrolment in March 2014.

## Abbreviations

CES-D: Center for Epidemiological Studies Depression
DOT: directly observed therapy
DR: drug resistant
IRB: institutional review board
MDR-TB: multi-drug resistant TB
NTC: National Tuberculosis Control Center
SMS: short message service
TB: tuberculosis
WHO: World Health Organization
XDR: extensively drug-resistant
